## 6. Recruitment Methods

### 6.1. Does the study involve the recruitment of participants?

☐ No: If no, skip to 7.1

☒ Yes: If yes; indicate how, when, where, and by whom participants will be recruited

**6. How:** Up to 1000 IFD members with permanent station assignments at one of the 44 Indianapolis fire houses will be recruited. The initial approach will be through a written announcement from the Chiefs of the Indianapolis Fire Department (IFD)/ Fishers FD and the firefighters' local union presidents (see attached letter) informing the IFD/ Fishers FD of the inauguration of the study and their opportunity to voluntarily participate. Next, human subjects-trained staff from Public Safety Medical (PSM) will visit each fire house to approach IFD/Fishers members for informed consent and determine their eligibility. Their recruitment script is attached. IFD/ Fishers members eligible for study consent and participation will include those: a) permanently assigned to one of the 44 IFD stations or one of 6 Fishers stations; b) with a fire department medical in the last two years; c) at least 18 years of age; and d) full, modified or restricted duty status at randomization; OR e) Firefighters categorized as "Administrative Staff" by the IFD/ Fishers will also be approached for participation. The fire department will notify PSM regarding criteria a, c, d and e and PSM has a record b (medical exams). First, they will provide a brief overview of the study to the firefighters by reiterating the information from the Chief and Union President's letter and the approved informed consent form. They will inform the fire house of its intervention assignment in the study – in other words, whether they will be receiving the nutritional intervention immediately (In Phase 1); or after 12 months (Phase 2). Next, each member will be offered an informed consent form to review on his/her own and will be allowed at least 15 minutes and longer if desired to review it on their own and to discuss it with their colleagues or others. Finally, each member will have a chance to ask the PSM staff questions individually in private areas of the fire house and may decide to sign the form or decline. IFD/Fishers members will be assured that participation status in the study is completely voluntary and will have no bearing on their employment with the department or on the occupational health care they receive from PSM. Consented participants will be assigned to the Phase 1 nutritional intervention (Group 1) or No intervention (Group 2) according to their fire station's cluster randomization. "Administrative" firefighters who consent will be assigned to Group 1 because they are not assigned to specific fire houses. For the biomarkers study randomly 100 participants (50 in each group) will be invited to participate in the study via email at the same time as the follow-up reminder. The recruitment will stop when we reach 60 participants (30 in each group)

**When:** Recruitment will begin as soon as possible following the study's approval by the IRB with the Fire Chief and Union President letter being sent out to all department members. In person recruitment as described above will follow shortly thereafter, on a schedule to visit all 44 IFD / 6 Fishers fire

stations during regular business hours as many times as needed to approach all members with potential interest. For the biomarkers study recruitment will start by the end of December 2017/January 2018. We expect this process to take 4-8 weeks.

**Where:** The Fire Chief and Union President letter will be sent by mail and email to IFD /Fishers members. The in-person recruitment will take place in each fire station as described above. The PSM researchers will then be visiting each IFD / Fishers fire station to speak with the firefighters about the study and offer them the opportunity to participate. These discussions will take place in common areas of the fire houses such as kitchen/dining area and living rooms, while the individual consenting and question/answer will take place in areas of the fire house that provide privacy.

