## 1. Specific Aims

1. Develop a multi-pronged, Mediterranean Diet Nutritional Intervention (MDNI) behavior change strategies including: diet/lifestyle education; discounted access to key Mediterranean diet foods; electronic education platforms and reminders. MDNI components will be refined via surveys, literature review and local/national firefighter input including labor/management and fire service focus groups.

Hypothesis (1). Cost-effective, fire-service MDNIs will be developed for the cluster-randomized, career firefighter diet intervention.

2. Cluster Randomized Diet Intervention-Phase I- the Indianapolis Fire Department (IFD) has over 1,000 members. All 44 IFD firehouses will be cluster randomized into two groups and then individual members will be consented regarding study participation. Group 1 will receive an active 12-month MDNI, while Group 2 will receive no intervention. Firefighters categorized as "Administrative Staff" by the IFD will also be approached for participation and if they consent, be assigned to Group 1 because they are not assigned to specific firehouses.

3. Cluster Randomized Diet Intervention -Phase II: Group 1 will cross-over to "self-sustained continuation" for 12 months to examine persistence of behavior change during this less intense, self-directed maintenance diet intervention. Group 2 will cross-over to receive the MDNI for 6 months (assessing a shorter MDNI), followed by a final 6 months of self-sustained continuation. An additional neighboring fire department, Fisher's (IN), will have its 6 firehouses randomized to receive the MDNI (Group 3) or no intervention (Group 4) for six months, and then individual members will be consented regarding study participation. After 6 months, the 3 stations in the MDNI (Group 3) will cross-over to "self-sustained continuation" for the last 6 months to examine persistence of behavior change during this less intense, self-directed maintenance diet intervention. Group 4 will cross-over to receive the MDNI for 6 months (assessing a shorter MDNI).

4. A similar 12-month Cluster Randomized Diet Intervention in the six fire stations of the Fishers (IN) Fire Department with a cross-over by the control group to intervention after 6 months will also be done.

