##### Baseline Assessment:

- Using established coded data transfer methods between Public Safety Medical and the Harvard TH Chan School of Public Health. Public Safety Medical will transfer the results of the last existing fire department medical examination to the Harvard Chan research team for consented participants only.
- Medical exam data that will be provided to the study team for consented IFD/ Fishers subjects include: at rest and maximal heart rate, systolic and diastolic blood pressure, heart rate recovery, electrocardiographic findings at rest, hip and waist circumference, body composition, data regarding the grip strength, leg-press and push-ups performed, and routine lab values (e.g. lipid panels, hs-CRP and glucose).
- The medical exams will be supplemented by a comprehensive nutritional-lifestyle questionnaire (see attached). The survey instrument combines our existing mMDS with other validated scores and nutrition questionnaires. It also includes items on physical activity and other health behaviors to adjust for appropriate covariates. These questionnaires will be self-administered online via Qualtrics on a password-protected site. The comprehensive nutritional-lifestyle questionnaire should take between 20-45 minutes to complete.

In addition, the baseline assessment will include anthropometric measures (height, weight and body fat estimates (Tanita) and resting blood pressure will be taken in private areas of the fire houses by trained Public Safety Medical clinical staff, during work hours. Height will be measured in the standing position with a standard clinic stadiometer. Waist circumference will be assessed by using a tape measure snugly around each participant’s waist at the level of the iliac crests and measuring the circumference after expiration. Body weight will be measured with bare feet and in light clothes on a calibrated scale. Body fat will be estimated using a Bioelectrical Impedance Analyzer (Tanita). Blood pressures will be measured using an appropriately sized cuff with the subject in the seated position in a resting state.

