## 9. Consent Process

- e. Will consent to participate be obtained?

☐ No: If no, skip to i

☒ Yes: If yes; describe the setting, role of individuals involved, timeframe(s), and steps to minimize coercion/undue influence during the consent process (at the time of initial consent and throughout the study)

Consent to participate will be obtained prior to any study participation. Human subjects-trained staff from Public Safety Medical (PSM) will visit each fire house to approach eligible IFD / Fishers FD members for informed consent. First, they will provide a brief overview of the study to the firefighters by reiterating the information from the Chief and Union President's letter and the approved informed consent form. IFD /Fishers members will be assured that participation status in the study is completely voluntary and will have no bearing on their employment with the fire department or on the occupational health care they receive from PSM. This assurance is reiterated in both Chief's /Union President's letter and the approved informed consent form. Each member will be offered an informed consent form to review on his/her own. Finally, each member will have a chance to ask the PSM staff questions individually in private areas of the fire house and may decide to sign the form or decline without any pressure from other firefighters. Participants are reminded throughout the study of their rights to withdraw at any time of the study. Any new information which might influence a participant's decision to continue participation will be provided to participants, including re-consent where applicable.

- f. Are there any special populations?

☒ No ☐ Yes: If yes; describe the process to obtain consent, permission or assent

- g. Will consent of the participants be documented in writing?

☒ Yes ☐ No: If no; describe the rationale for requesting a waiver or alteration of documentation of consent (and/or parental permission)

- h. Will participants be provided with a copy of their signed consent form or information sheet (when a consent form is not signed)?

☒ Yes ☐ No: If no; explain any extenuating circumstances that make it impossible or inappropriate to meet this requirement, i.e., doing so may place participants at increased risk, if inadvertently disclosed

- i. Is a waiver or alteration of consent (and/or parental permission) being requested?

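### Fire houses are told their arm before members are asked to consent, so enrolment, the self-reported baseline diet score and the station measurements all happen with allocation known

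*Protocol*

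**What the plan says.** Section 1 (Specific Aims) fixes the order for Indianapolis: "All 44 IFD firehouses will be cluster randomized into two groups and then individual members will be consented regarding study participation". It gives the same order for the six Fishers stations, which are randomised to the programme or to no intervention "for six months, and then individual members will be consented regarding study participation".

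Section 6.1 describes the recruitment visit. After a short overview, staff tell the house whether it gets the programme at once or after 12 months: "They will inform the fire house of its intervention assignment in the study". The next step is "Next, each member will be offered an informed consent form to review on his/her own", with time to talk it over with colleagues. At the end each member "may decide to sign the form or decline".

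Section 9 adds: "Consent to participate will be obtained prior to any study participation". The baseline assessment in section 4.6 has three parts:
- results of the last existing fire department examination, transferred for consented members;
- the nutrition and lifestyle questionnaire that contains the mMDS: "These questionnaires will be self-administered online via Qualtrics on a password-protected site";
- weight, body fat, waist and blood pressure, taken at the station by the occupational health contractor's clinical staff. The same contractor does the recruiting.

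Section 5.1 compares the groups by intention to treat according to each participant's fire house, using repeated-measures models adjusted for baseline and time-dependent covariates.

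**The concern.** Randomising stations makes the full station memberships comparable in expectation. It does not do so for the subset who choose to join after hearing their arm. Willingness to sign may depend on whether the programme starts now or a year later, and the kind of member who signs may then differ between arms. Intention to treat keeps every enrolled member in the arm of the station, but it cannot restore members who declined.

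There is a second route. The mMDS is self-reported and is the first outcome for which section 5.2 calculates power. Members answer the baseline questionnaire knowing whether a diet programme is about to start, so the answers themselves may shift by arm. That baseline feeds both the change from baseline and the covariate adjustment.

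At stake is the randomised comparison of the programme with no intervention in Phase I, and the corresponding comparison in the Fishers stations.

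**Working it through.** The plan states no figure on this point, so the first check is the order of events.

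1. Stations are randomised (section 1).
2. The house is told its arm (section 6.1).
3. The consent form is offered, and each member signs or declines (section 6.1).
4. Study procedures begin (section 9): baseline questionnaire and station measurements (section 4.6).

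No section holds the assignment back until step 3 or 4 is complete. One baseline component falls outside the sequence: the examination transferred under section 4.6 already exists, so knowing the arm cannot change its values. It is transferred for consented members only, so step 3 still decides who contributes it.

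**Size of a baseline imbalance (illustration).** Let q be the share declining and D the mean of joiners minus the mean of decliners, in SD units. The station population mean is (1 - q) x joiner mean + q x decliner mean, so joiners differ from their population by q x D. Randomisation gives both arms the same population mean in expectation. With the same D in both arms, the gap between enrolled groups has size (q2 - q1) x D.

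Inputs from the documents: SD 5.6 for mMDS and 6.6 for body fat (section 5.2), and about 90% consent in an earlier imaging study in the same department (section 7.1). Assumptions, not in the documents: consent in the delayed arm, and D of 0.25 to 0.5.

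| Consent, immediate vs delayed | Gap in SD, D = 0.25 to 0.5 | mMDS points | Body fat points |
|---|---|---|---|
| 90% vs 90% | 0 x D = 0 | 0 | 0 |
| 90% vs 75% | 0.15 x D = 0.04 to 0.08 | 0.21 to 0.42 | 0.25 to 0.50 |
| 90% vs 70% | 0.20 x D = 0.05 to 0.10 | 0.28 to 0.56 | 0.33 to 0.66 |

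A second parametrisation takes the delayed-arm joiners as a core and lets the extra joiners in the immediate arm differ from that core by D. The gap is then (r1 - r2)/r1 x D, where r is the consent rate. For 90% vs 75% this is 0.167 x D = 0.04 to 0.08. For 90% vs 70% it is 0.222 x D = 0.06 to 0.11. Both versions give roughly 0.05 to 0.1 SD. The direction depends on who declines, and sample size does not enter either formula.

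The zero in the first row needs the same kinds of members to join in both arms. Equal consent rates alone do not guarantee it, because D may differ by arm.

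**Arm-aware self-report.** If knowing the arm moves reported baseline mMDS in one arm by d points, change from baseline in that arm moves by -d. A model adjusting for the reported baseline moves by about -b x d, where b is the slope of follow-up on baseline. The documents give nothing from which to estimate d.

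**The case against.** The strongest reply is that section 5.1 adjusts for baseline and analyses change. A stable baseline gap in a measured outcome largely drops out of such an analysis. That stands, and it rules out a tempting stronger reading. From 90% vs 75% consent and D = 0.5 SD (3.3 body fat points), a reader might set 0.15 x 3.3 = 0.495 points against the planned 1.7-point effect and infer that 29% of the effect could be bias. The documents do not support that: 0.495 is a gap at baseline, resting on assumed inputs, and it is not the error left after adjustment. What adjustment leaves is any difference in motivation or response that the covariates do not capture, plus any distortion of the reported baseline, which is itself the adjuster.

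Section 7.1 offers two further mitigations: everyone who consents gets the programme at some point, and about 90% consented in the earlier study. Both make differential enrolment less likely. Neither settles it. A wait of 12 months is still a difference when the member decides, and the earlier rate came from a different study and says nothing about consent by arm here. Section 4.3 also accepts as few as 500 participants from a department of over 1,000. Neither mitigation touches the baseline questionnaire.

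A reader might also infer that randomisation has lost all force, or that every baseline value is compromised. Neither follows. Stations remain randomly allocated and members are analysed by station; selection within stations is what is exposed. Body fat and weight are measured rather than self-reported, and the pre-existing examination values are fixed.

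**Conclusion.** The concern holds as a risk built into the visit order. Enrolment, the baseline mMDS questionnaire and the station measurements all follow disclosure, and the main comparison is confined to members who consented knowing their arm. The documents do not show that a difference arose, and its size cannot be derived from them. The illustrated imbalance of roughly 0.05 to 0.1 SD rests on the assumed consent rates and decliner differences. The residual bias in the adjusted effect is not quantified. The point still warrants a change, because analysis cannot repair selection on unmeasured factors, whereas reordering the visit prevents much of it at little cost.

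**What to change.** **Stations not yet recruited, including any Fishers stations still to be recruited.** Reorder the visit in section 6.1:
1. Tell members that the house will receive the programme either now or later. This is truthful, because all who consent receive it eventually. It also suits Fishers, where section 1 gives a wait of 6 months rather than the 12 in section 6.1.
2. Obtain consent.
3. Complete the baseline questionnaire and station measurements.
4. Only then disclose the assignment.

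Flag members who join after disclosure and run a sensitivity analysis without them, in these stations only. Where the stated order was used, everyone consented after being told, so the same exclusion would empty the comparison.

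**Stations already recruited under the stated order.** This may be most or all of Indianapolis: section 4.6 places the 1-year follow-up at the biomarker baseline, dated December 2017/January 2018. Recruitment status itself is not stated. For these stations:
- report consented over approached, by arm;
- report baseline values by arm, including the pre-existing examination values;
- adjust for those examination values, which the arm could not have influenced;
- describe the comparison as open to post-randomisation recruitment bias.

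**Cost.** A change of visit order and recruitment wording, notified to the IRB as section 22 requires, and a log of members approached. Disclosure and programme start in each house wait until its enrolment visits and baseline are done. Randomisation is unchanged.

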**6.2. Are there any materials that will be used to recruit participants, e.g., emails, posters, and scripts?**

☐ No ☒ Yes: If yes; provide a list of the materials (also include copies with the application)

The attached Fire Chief and Union President letter with letters from national fire service organizations that endorse our study (IAFF and NFFF) attached, as well as the "Public Safety Medical" script.

**7. Available Resources**

**7.1. Describe the feasibility of recruiting the required number of participants within the recruitment period**

The recruitment process is highly feasible. Previously, we have been very successful in participant recruitment from the Indianapolis Fire Department (IFD). In a study of cardiac imaging now completed within the IFD, about 90% of IFD members approached consented and completed the study. We have also worked successfully with Fishers FD in the past on imaging studies. Additionally, the proposed research will succeed in large part due to the solid fire service partner commitments. *Indianapolis Fire Department* (IFD), Fishers FD and *Indianapolis Local 416* support is crucial for recruiting participants and for conducting. Furthermore, the research proposal has been endorsed by significant national fire service partners, which should increase trust and willingness to participate. Moreover, our study designs are such that all firefighters who consent will receive the Mediterranean Diet Nutritional Intervention at some point and have an opportunity for health benefits. Therefore, we expect no problems identifying and recruiting the necessary participants.

**7.2. Describe how the Principal Investigator will ensure that a sufficient amount of time will be devoted to conducting and completing the research**

This project will be conducted as sponsored research and a grant has been awarded to the PI by the US Department of Homeland Security. The PI is devoting at least 10-15% of his effort to this project through the above award from September 2016 on. The PI and his team will also be continuing weekly meetings with our colleagues in Indianapolis to ensure that the study proceeds as close as possible to its proposed timeline.

**a. Briefly describe how the research facilities and equipment at the research site(s) support the protocol's aims, e.g., private rooms available for interviews, etc.**

Harvard and its affiliated facilities provide full managerial, administrative and statistical expertise and software, as well as world-class computational, electronic and physical library facilities to support the proposed research.

In Indianapolis, each fire station has the facilities required to support the protocol's aims. Each fire station has rooms with audiovisuals for the group sessions, full kitchen facilities for cooking demonstrations and regular meal preparation, and private areas for conducting the informed consent process and assessing weights and blood pressures.

**b. Are there provisions for medical and/or psychological support resources (e.g., in the event of incidental findings, research-related stress)?**

☐ No ☒ Yes: If yes; describe the provisions and their availability

Public Safety Medical may provide psychological services as needed or referrals to other resources in the community in the unlikely event of stress resulting from incidental findings or other research-

related stress.

## 8. Vulnerable Populations

- c. Are there any potentially vulnerable populations (e.g., children, pregnant women, human fetuses, neonates, prisoners, elderly, economically disadvantaged, employees or students of the investigator or sponsor, undocumented, terminally ill, cognitively impaired or mentally ill, etc.)?

☒ No: If no, skip to e

☐ Yes: If yes; identify all vulnerable populations

- d. Describe safeguards to protect their rights and welfare

N/A.

